### Trial procedures and study interventions

Recruitment and enrollment for this study will be from the institution’s local practice or referrals from other physicians. All trial-related procedures and interventions will be performed according to the predefined schedule of events (Table 1). Before any study-related procedure, each patient will provide written informed consent, unless that procedure was performed as part of the patient’s standard medical care and is eligible for trial enrollment. Prior to study treatment a screening period, no longer than 28 days, will be considered. During this period, eligibility will be assessed and tumor tissue procured for biomarker analysis. Eligible patients will be randomly allocated to an experimental arm (arm A), which will test the addition of lapatinib to radiochemotherapy with capecitabine or a control arm (arm B), which will consist of standard radiochemotherapy with capecitabine. Patients allocated to arm A will undergo an initial lead-in period of 14 days with lapatinib before radiochemotherapy. At the end of the lead-in period, patients in arm A will have a tumor biopsy performed for biomarker assessment. As lapatinib is a substrate for CYP3A4, inducers and inhibitors of this enzyme are prohibited from screening through discontinuation from study, and a predefined wash-out period prior to random allocation has been set (Table 2). Seven to eight weeks after completion of radiochemotherapy, patients will be surgically treated. For the duration of the trial, no other concurrent anticancer therapy or investigational agents are allowed. During the trial, neither patients nor treating physician will be blinded to treatment interventions.

**Table 1 Tab1:** Schedule of events

	Screening	Random allocation (^a^)	Treatment period								EOT	Surgery	EOS
			Day -14 (^b^)	Day -7	Day 1 (^c^)	Day 8 ± 3 days	Day 15 ± 3 days	Day 22 ± 3 days	Day 29 ± 3 days	Day 36 ± 3 days	Day 66 ± 3 days	Day 87–94	28 (+7) days after surgery
Informed consent	X												
Inclusion/exclusion criteria	X	X											
Demographics	X												
Medical history	X												
Concomitant medications	X	X		X	X	X	X	X	X	X	X		X
Adverse events				X	X	X	X	X	X	X	X		X
Physical examination	X	X											
Vital signs	X	X		X	X	X	X	X	X	X	X		X
Weight	X	X		X	X	X	X	X	X	X	X		X
Height	X												
ECOG performance status	X	X		X	X	X	X	X	X	X	X		X
Electrocardiogram (12-lead)	X										X		X
MUGA	X										X		X
Hematology	X	X		X	X	X	X	X	X	X	X		X
Serum chemistries	X	X		X	X	X	X	X	X	X	X		X
Hemostasis	X												
Pregnancy test	X										X		X
CT – scan (chest, abdomen, pelvis)	X												
Endoscopic ultrasound	X												
Tumor sampling	X				X(^c^)							X	
Lapatinib (arm A)			1 250 mg/d until the last day of radiotherapy										
Capecitabine (arms A and B)					825 mg/m2 twice daily from first to last day of radiotherapy								
Radiation therapy					50.4 Gy in 28 fractions of 1.8 Gy, 5 days per week								

*EOT* end of treatment visit, *EOS* end of study visit

(^a^) Within 4 weeks of screening visit

(^b^) Not more than 3 days before day -14 in arm A or more than 14 days before day 1 in arm B. In arm B, random allocation visit procedures are valid for day 1 visit if <7 days have elapsed

(^c^) Arm A only: to be performed within a 3-day time window of day 1 of radiation treatment

**Table 2 Tab2:** CYP3A4 inducers and inhibitors

Drug class	Agent	Wash-out
CYP3A4 inducers		
Antibiotics	All rifamycin agents (e.g., rifampicin, rifabutin, rifapentine)	14 days
Anticonvulsants	Phenytoin, carbamazepine, barbiturates (e.g., phenobarbital)	
Antiretrovirals	Efavirenz, nevirapine	
Glucocorticoids (oral)	Cortisone (>50 mg), hydrocortisone (>40 mg), prednisone (>10 mg), methylprednisone (>8 mg), dexamethasone (>1.5 mg)	Not Applicable
Others	St. John’s wort (*Hypericum perforatum*), modafinil	Not Applicable
CYP3A4 inhibitors		
Antibiotics	Clarithromycin, erythromycin, troleandomycin	7 days
Antifungals	Itraconazole, ketoconazole, fluconazole (>150 mg/d), voriconazole	
Antiretrovirals, protease inhibitors	Delavirdine, nelfinavir, amprenavir, ritonavir, indinavir, saquinavir, lopinivir	
Calcium channel blockers	Verapamil, diltiazem	
Antidepressants	Nefazodone, fluvoxamine	
GI agents	Cimetidine, aprepitant	
Others	Grapefruit, grapefruit juice	
	Amiodarone	6 months
Miscellaneous		
Antacids	Mylanta®, Maalox®, Tums®, Rennie®	1 h before and after dosing
Herbal or dietary supplements	Ginkgo biloba, grape seed, valerian, ginseng, echinacea, evening primrose oil	14 days

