#### Inclusion criteria

Each patient must meet all of the following inclusion criteria to be enrolled in the study:Age of 18 years or aboveDiagnosis of adenocarcinoma of the rectum with the primary malignant lesion located between the dentate line up to 10 cm of the anal verge by endoscopic examinationAbsence of activation mutation in KRAS exons 2 (codons 12 and 13), 3 (codons 59 and 61), and 4 (codons 117 and 146) and NRAS exons 2 (codons 12 and 13), 3 (codons 59 and 61), and 4 (codons 117 and 146)Clinical stage II or III disease, according to American Joint Committee on Cancer Staging classification, 7th edition [40]. For clinical staging, the following procedures must have been conducted within 4 weeks of treatment allocation:Clinical history and physical examinationEndoscopic ultrasound of the primary lesionThoracic, abdominal, and pelvic computed tomographic (CT) scanClinically judged to be able to undergo curative resection of the rectal neoplasm despite preoperative radiochemotherapyClinically judged to be able to undergo pelvic radiation therapy to a total dose of 50.4 GyProvision of signed informed consent

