#### Lapatinib

Lapatinib, 250-mg tablets, will be self-administered, on an empty stomach (either 1 h before or after a meal), with water, once daily at approximately the same time each day, at a dose of 1250 mg/d. Treatment with lapatinib will be initiated 14 days prior to radiation therapy (lead-in period) and continued for the duration of radiation therapy. Patients will be instructed not to take lapatinib with grapefruit or grapefruit juice. Moreover, patients will be instructed that if they vomit any time after taking a dose, they must not “make it up” with an extra dose, but instead resume dosing with the next scheduled daily dose. Any missed dose will not be replaced; the dosing should resume with the next scheduled daily dose. Patients will be required to return all used, unused, and/or partially used bottles of lapatinib, and the number of remaining tablets will be documented and recorded to assess compliance.

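### Eligibility is re-checked at random allocation without a new pregnancy test, so the pregnancy exclusion rests there on a screening result up to 28 days old, and the article leaves unclear where the 28-day window ends

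*Protocol article*

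**What the plan says.** Under Exclusion criteria, the protocol article bars pregnant women. It also bars fertile patients who will not or cannot use effective contraception. Trial procedures and study interventions makes the schedule in Table 1 binding for all trial procedures.

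In Table 1:

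- The row "Inclusion/exclusion criteria" is marked at screening and again at random allocation. Hematology and serum chemistries are repeated at allocation too.
- The row "Pregnancy test" is marked at screening, end of treatment and end of study only.
- Footnote a times random allocation: "Within 4 weeks of screening visit".
- Footnote b adds the interval between allocation and treatment: "Not more than 3 days before day -14 in arm A or more than 14 days before day 1 in arm B". It also limits how long allocation-visit results stay usable: "In arm B, random allocation visit procedures are valid for day 1 visit if <7 days have elapsed".

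The 28 days appear in two other places. Inclusion criteria says of the staging work-up that "the following procedures must have been conducted within 4 weeks of treatment allocation". The text before Table 1 says: "Prior to study treatment a screening period, no longer than 28 days, will be considered".

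**The concern.** The second eligibility check is there to catch changes since screening. For blood counts and chemistry, Table 1 supplies fresh results at that visit. For pregnancy, which is just as absolute an exclusion, it supplies none. A conception after screening that is not yet recognized could pass the re-check and be followed by study drugs and pelvic radiation. The next scheduled test is at end of treatment, after all radiation has been given.

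The windows add a second problem. The inclusion criterion on staging and footnote a tie the four weeks to allocation, whereas the running text refers to the time before study treatment. A site cannot tell from the article whether a patient allocated on day 28 and treated later is still inside the screening period. If the window runs to first treatment, the answer also depends on the arm drawn, which is unknown at screening.

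**Working it through.** The article gives no maximum age for the pregnancy test, so there is no stated figure to reproduce. The check adds up the longest permitted intervals.

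**Inputs**

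- Screening to random allocation: at most 28 days (Table 1, footnote a).
- Allocation to first lapatinib at day -14, arm A: at most 3 days (footnote b).
- First lapatinib to first radiation, arm A: 14 days (section Lapatinib, lead-in period).
- Allocation to day 1, arm B: at most 14 days (footnote b).
- Alternative limit: 28 days from screening to first study treatment (one reading of Trial procedures and study interventions).

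**Reading 1: the 28 days end at allocation, and footnotes a and b apply as written**

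Maximum age of the result = sum of the permitted intervals.

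- At the eligibility re-check, both arms: 28 days.
- Arm A, first lapatinib: 28 + 3 = 31 days.
- Arm A, first capecitabine and radiation: 28 + 3 + 14 = 45 days.
- Arm B, first capecitabine and radiation: 28 + 14 = 42 days.

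**Reading 2: the 28 days end at first study treatment**

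- Arm A, first lapatinib: 28 days.
- Arm A, first capecitabine and radiation: 28 + 14 = 42 days.
- Arm B, first capecitabine and radiation: 28 days.

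**Comparison**

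| Time point | Reading 1 | Reading 2 | Difference |
|---|---|---|---|
| Arm A, first lapatinib | 31 | 28 | 3 |
| Arm A, first radiation | 45 | 42 | 3 |
| Arm B, first radiation | 42 | 28 | 14 |

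The two readings differ by 3 days in arm A and 14 days in arm B. In arm A the result can be six weeks old or more at first radiation on either reading. The figures for first treatment and first radiation do not describe the eligibility re-check. That takes place at allocation, where the result is at most 28 days old, and Table 1 marks no further check of eligibility at day 1.

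**The case against.** The case on the other side has several parts.

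- **The exclusion has other support.** A reader might infer that it cannot be verified at the re-check. The documents do not support that. The result is then at most 28 days old, fertile patients must accept effective contraception, a physical examination is done at allocation, and a pregnancy known by then would exclude the patient. This stands. What remains is that no current test supports the re-check; the contraception criterion lowers the risk but does not confirm the patient's status.
- **No limit on test age is broken.** A reader might take 28 days as the permitted age of the test and conclude that Table 1 exceeds it. The 28 days in the running text limit the screening period, not the test. The excess of 3 or 14 days arises only if that period runs to first treatment. On that reading, the maxima at radiation are themselves lower. Because the text goes on to say that eligibility is assessed within this period and eligible patients are then allocated, the period may well end at allocation, in agreement with the staging criterion and footnote a. This also stands; the passages can be read differently, but they do not plainly collide.
- **The analysis sets are not shown to be affected.** A reader might expect window deviations that differ by arm to remove patients from the exploratory subgroup population. Nothing in the article classes a patient scheduled within footnotes a and b as a major violation, and the intention-to-treat, per-protocol and safety populations do not depend on screening windows.
- **The full protocol is not shown** and may contain further testing instructions. That is possible. However, the article prints a complete schedule and declares it binding, so the mismatch between the two rows lies in the text at hand.

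**Conclusion.** The point holds, at low severity. The eligibility re-check at allocation has no pregnancy test of its own and relies on a result up to 28 days old plus the contraception criterion. Under footnotes a and b that result can be 42 days old at first treatment in arm B. In arm A it can be 31 days old at first lapatinib and 45 days old at first radiation. If the 28 days run to first treatment, the maxima at first radiation are 28 days (arm B) and 42 days (arm A). The article does not settle which reading applies.

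This rests on four assumptions: the test is done on the day of the screening visit; every interval is used to its limit; footnote b, by its wording, governs the time from allocation to treatment; and the lead-in counts as exactly 14 days. It is also assumed that few patients in this population are of childbearing potential; the article gives no age distribution. The issue is one of patient safety in a few women, and no effect on the primary analysis is claimed.

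**What to change.** Two reconciliations are needed.

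1. Bring the pregnancy-test row of Table 1 into line with the eligibility re-check at random allocation, so that for women of childbearing potential the exclusion is supported by a current result at that existing visit.
2. Reconcile the staging criterion under Inclusion criteria, the screening-period sentence in Trial procedures and study interventions, and footnotes a and b, so that all state one end point for the 28-day window. Which end point to use is for the sponsor and the investigators to decide.

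The cost is one extra laboratory test in a small subset, at a visit that already includes laboratory work, plus a wording change. No extra visit or patient is needed. The first change shortens the gap without closing it: a result obtained at allocation could still be 14 days old at first radiation in arm B and 3 + 14 = 17 days old in arm A.

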#### Lapatinib

Lapatinib, 250-mg tablets, will be self-administered, on an empty stomach (either 1 h before or after a meal), with water, once daily at approximately the same time each day, at a dose of 1250 mg/d. Treatment with lapatinib will be initiated 14 days prior to radiation therapy (lead-in period) and continued for the duration of radiation therapy. Patients will be instructed not to take lapatinib with grapefruit or grapefruit juice. Moreover, patients will be instructed that if they vomit any time after taking a dose, they must not “make it up” with an extra dose, but instead resume dosing with the next scheduled daily dose. Any missed dose will not be replaced; the dosing should resume with the next scheduled daily dose. Patients will be required to return all used, unused, and/or partially used bottles of lapatinib, and the number of remaining tablets will be documented and recorded to assess compliance.

#### Capecitabine

Capecitabine, 150-mg tablets and 500-mg tablets, will be self-administered at a dose of 825 mg/m^2^ (dose rounded to the nearest possible combination of the available tablet formulations) twice daily, within 30 minutes of a meal, with water, for the duration of radiotherapy. Patients will be required to return all used, unused, and/or partially used blister packs of capecitabine at the next study visit. The number of tablets remaining will be documented and recorded to assess compliance.

#### Radiation therapy

Patients will be treated with megavoltage energy to a total treatment dose of 50.4 Gy to the clinical target volume. This treatment will be administered in 1.8-Gy daily fractions, 5 days per week. The treatment technique will be decided by a senior radiotherapist with expertise in rectal cancer treatment. The following techniques will be available: 3D conformal external beam radiation (3D-RT), intensity modulated radiotherapy (IMRT), and volume modulated arc therapy (VMAT). The choice of technique will depend on the need to protect the organs at risk for increased toxicity with radiation treatment based on the planning CT scan. The planning CT scan will image the lower abdomen and pelvis, from first lumbar vertebra to 3 cm below the buttocks soft tissue projection, with 2.5-mm-thick slices. For both the planning CT scan and treatment, the patient will be in a supine position, with head and knee support and hands resting on the thorax with the bladder comfortably full [41]. Volume delineation and dose prescription will be done according to the guidelines set forth by International Commission on Radiation Units (ICRU) Reports 50 and 62 for 3D-RT and ICRU Report 83 for IMRT or VMAT. The primary tumor and regional lymph nodes will be included in the treatment volumes [42–44]. The following volumes will be considered: gross tumor volume (GTV), which includes the rectal tumor and suspicious lymph nodes; clinical tumor volume 45 Gy (CTV45), which includes the rectal tumor and the regional lymph nodes (delimited superiorly by the common iliac arteries bifurcation and inferiorly by the obturator canal); the planned target volume 45 Gy (PTV45), which includes the CTV45 with a 1-cm external margin except when that margin is the skin; the clinical tumor volume 50.4 Gy (CTV50.4), which includes the GTV and the entire mesorectum and presacral region at involved levels and a 2-cm cephalad and caudal margin beyond any suspicious lymph node, and for tumors located at the anorectal junction, the CTV50.4 will include the GTV and a 1-cm anterolateral and posterior margin in addition to the above mentioned cephalad and caudal margin; and the planned target volume 50.4 Gy (PTV50.4), which includes the CTV50.4 with a 1-cm margin, except at the skin.

During treatment planning the following organs will be considered at risk of unacceptable toxicity during pelvic radiation: bladder, small intestine, and femurs (head of femur). To protect against this risk, during treatment planning, dose-volume histograms for these organs will be independently calculated to ensure that the dose constraints set forth in Table 3 for each of the organs at risk are abided by [45–47].

**Table 3 Tab3:** Dose-volume constraints

Organ at risk	Dose restriction
Bladder	V40 < 50 %
	V45 < 30 %
Small intestine	No more than 180 cc above 35 Gy
	No more than 100 cc above 40 Gy
	No more than 65 cc above 45 Gy
Femoral head	V25 < 45 %
	V40 < 40 %
	V50 < 10 %

#### Surgery

For all included patients, surgical treatment will be performed 7 to 8 weeks after the end of radiation therapy. The choice of surgical technique will depend on preoperative assessment by a senior surgeon trained in rectal cancer surgery. Total mesorectum excision will be recommended.

#### Management of trial interventions

During treatment, all patients will be observed weekly to assess toxicity. Patients are allowed to receive full supportive care therapies concomitantly during the study. Summary recommendations for dose modification due to treatment emergent adverse events are defined and outlined in Table 4. No individual lapatinib dose reduction or dose escalation will be allowed to manage treatment-related adverse events. In the event of excess toxicity at a dose level of 1250 mg/d of lapatinib, the trial will be stopped and restarted with lapatinib dosed at 1000 mg/d. If a patient requires holding of radiation treatment for 2 or more weeks to manage any adverse event, radiation treatment will be discontinued. In case of radiation treatment interruption, the total dose will be adjusted according to a biological equivalent dose calculation [48]. Any of the study interventions (lapatinib, capecitabine, and radiation therapy) may be discontinued if a patient experiences treatment emergent adverse events judged by the investigator to outweigh its benefits. Treatment with the study drug may be discontinued for any of the following reasons: protocol violation, study termination by the sponsor, loss to follow-up, or death. Additionally patients may discontinue therapy at any time.

**Table 4 Tab4:** Summary of dose modification guidelines

Adverse event (CTCAE v4.0)	Lapatinib	Capecitabine	Radiation
Hematology: neutrophils or platelets			
Grade –2:	Continue	Hold 7 days^a^	Continue
Grade ≥3:		Hold 7 days^a^	Hold^b^
Dermatology: rash			
Grade –3:	Hold 7 days^a^	Not applicable	
Dermatology: irradiated skin			
Grade ≥3:	Not applicable		Hold^b^
Dermatology: palmar-plantar erythrodysesthesia			
Grade ≥2:	Not applicable	Hold 7 days^a^	Not applicable
Gastroenteroloy: diarrhea			
Grade ≥3:	Discontinue	Hold^a^	Hold^b^
Respiratory: pneumonitis			
Grade ≥3:	Discontinue		
Cardiac dysfunction:			
Asymptomatic LVEF decrease >20 % from baseline and absolute value below the LLN	Discontinue	Not applicable	
Grade –3			
Hepatotoxicity:			
ALT > 3 × ULN AND ALT < 5 × ULN	Continue	Not applicable	
ALT > 3 × ULN AND ALT > 5 × ULN for ≥2 weeks	Discontinue		
ALT > 3 × ULN AND ALT < 5 × ULN for > 4 weeks			
ALT > 3 × ULN AND bilirubin > 2 × ULN (>35 % direct)			
ALT > 3 × ULN AND ALT > 8 × ULN			
ALT > 3 x ULN AND signs and symptoms of hepatitis or hypersensitivity			

^a^Rechallenge if grade 0–1

^b^Restart if grade 0–2

Patients who discontinue any of the study drugs prior to surgical treatment may remain in the study and undergo radiation therapy (if this was not the cause of study drug discontinuation) and surgical treatment as per protocol. Patients who discontinue study drug due to a discontinuation of radiation therapy and are deemed surgically eligible will be surgically treated as per local standard of care. Patients who discontinue study drug will not be replaced.

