#### Follow-up

The end of treatment visit will be performed approximately 14 days after the last dose of radiochemotherapy. The end of study visit will be performed 30 days after the surgical intervention. In the event a patient develops any study-related toxicity, he will be followed until its resolution or clinical stabilization.

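### Table 4 stops lapatinib for a silent LVEF fall, but Table 1 plans no MUGA during the 52 to 54 dosing days; moving arm A's end-of-study scan to mid-treatment would narrow that gap

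*Protocol article*

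**What the plan says.** - **The rule.** Under Management of trial interventions, Table 4 has a cardiac row reading "Asymptomatic LVEF decrease >20 % from baseline and absolute value below the LLN". The action for lapatinib is to discontinue; capecitabine is marked as not applicable.
- **The measurement.** The exclusion criteria define LVEF by equilibrium radionuclide angiography. This is taken to be the MUGA row of Table 1.
- **The schedule.** The section Trial procedures and study interventions makes Table 1 the timetable for all trial procedures. Matched to the 13 visit columns, the MUGA row is marked at Screening, EOT and EOS. It is blank from random allocation through day 36.
- **The drug.** Table 1 gives lapatinib from day -14 at "1 250 mg/d until the last day of radiotherapy".
- **The later visits.** Table 1 puts EOT at day 66 ± 3. The Follow-up section says: "The end of treatment visit will be performed approximately 14 days after the last dose of radiochemotherapy". EOS is 28 (+7) days after surgery in Table 1 and 30 days after surgery in Follow-up.
- **Other monitoring.** "During treatment, all patients will be observed weekly to assess toxicity". Table 1 marks hematology and serum chemistries at day -7 and at every visit from day 1 to day 36. The 12-lead ECG has the same three visits as MUGA.

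**The concern.** The rule and the visit schedule are both printed, and they do not fit together. Table 4's blood-count rows have a matching test at each on-treatment visit, and so presumably do its ALT rows through serum chemistries. The LVEF row has none. If both tables are followed as written, an arm A patient whose LVEF falls silently past the threshold would finish lapatinib although Table 4 says to stop it.

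Acting on such a fall would cost the patient's trial participation little: "Patients who discontinue any of the study drugs prior to surgical treatment may remain in the study and undergo radiation therapy". What is at stake is the safety of individual arm A patients during dosing, not the comparison of pCR rates.

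**Working it through.** No power or sample-size formula applies. The check is a calendar count.

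**Inputs.** 28 fractions, 5 per week (Table 1); a 14-day lapatinib lead-in (Lapatinib section); surgery 7 to 8 weeks after radiotherapy (Surgery section); the EOT and EOS timings above. There is no day 0, and radiotherapy is assumed uninterrupted.

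**1. Last dosing day, checked against the plan's own figure.** From a Monday start, five full weeks give 25 fractions by day 33. The other three fall on days 36, 37 and 38. A Tuesday or Wednesday start also ends on day 38; a Thursday or Friday start ends on day 40. Surgery is then due from 38 + 49 = day 87 to 38 + 56 = day 94, exactly the window printed in Table 1. The protocol's own calendar thus ends radiotherapy, and lapatinib, on day 38.

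**2. Dosing days.** 14 + 38 = 52, or 14 + 40 = 54.

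**3. Planned scans against the last dose (day 38).**

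| Scan | Day | Days after last dose |
|---|---|---|
| EOT, Follow-up text | 38 + 14 = 52 | 14 |
| EOT, Table 1 | 63 to 69 | 25 to 31 |
| EOS, Table 1 | 87 + 28 = 115 to 94 + 35 = 129 | 77 to 91 |
| EOS, Follow-up text | 87 + 30 = 117 to 94 + 30 = 124 | 79 to 86 |

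With a day 40 finish, the Table 1 EOT is still 23 to 29 days after the last dose. Planned MUGA scans during dosing: 0. From first dose to first post-baseline scan is 14 + 52 - 1 = 65 days (text) or 14 + 66 - 1 = 79 days (Table 1; 76 to 82 over the window).

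**4. One scan at day 15 ± 3.** Dosing days before the scan = 14 + (scan day - 1). Dosing days left, counting the scan day = last day - scan day + 1.

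| Scan day | Before | Left, ending day 38 | Left, ending day 40 |
|---|---|---|---|
| 12 | 25 | 27 of 52 (52 %) | 29 of 54 (54 %) |
| 15 | 28 | 24 of 52 (46 %) | 26 of 54 (48 %) |
| 18 | 31 | 21 of 52 (40 %) | 23 of 54 (43 %) |

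These counts assume that the result is known on the day of the scan; any delay shortens what is left. A fall arising after the day 15 scan is next measured at EOT, 52 - 15 = 37 days later (text) or 48 to 54 days later (Table 1), after the last dose.

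**5. Choice of visit.** The documents give no onset timing, so it has to be assumed. Expected dosing days withheld per silent fall = share of falls arisen by the scan × days left. With uniform onset, day 15 gives 28/52 × 24 = 12.9, against 12.5 at day 8 and 11.4 at day 22. With late-weighted onset (share = (t/52)², where t is dosing days elapsed), day 22 is better (7.7 against 7.0). With early-weighted onset (share = √(t/52)), days 1 and 8 are better (19.7 against 17.6). Day 15 is a reasonable midpoint, and no more is shown.

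**The case against.** **Table 4 is a summary guideline.** It says what to do when an event is known and promises no scan. The article condenses a fuller protocol, which may set criteria for unscheduled MUGA. Part of this stands: an unscheduled scan can trigger the row, and weekly visits can pick up symptomatic cardiac events. A reader might infer that the rule can never operate or that cardiac safety goes unwatched; the documents do not support either. But a criterion defined by the absence of symptoms gives the weekly visit little to act on, so the mismatch between the printed tables remains.

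**The risk may be small.** Patients with LVEF below the institution's lower limit of normality (LLN) are excluded, the Discussion names diarrhea as the main anticipated toxicity, and no LVEF event rate is given. This stands, and it keeps the point minor.

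**The remedy trades one gap for another.** It gives up arm A's only planned LVEF reading after surgery. This also stands. A shorter longest interval between scans should not be claimed as the gain, because patients with normal readings would then have no planned measurement after EOT.

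**An arm A-only scan is not neutral.** Safety is the secondary endpoint, and "During the trial, neither patients nor treating physician will be blinded to treatment interventions". A fall found at the extra reading might be classed as a medically important condition and enter the arm A serious adverse event (SAE) count, which drives the toxicity stopping rule. The size of this effect is unknown, so it should be recognized in the amendment.

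**Conclusion.** The mismatch holds. On the planned schedule, all 52 to 54 lapatinib dosing days pass without an LVEF reading, and both post-baseline scans come too late to act on the asymptomatic criterion. This is so under either EOT definition and any weekday start, for uninterrupted treatment. A radiotherapy hold would lengthen dosing if lapatinib continued through it.

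The consequence is limited. It concerns silent falls in arm A only, and the benefit of a change cannot be quantified without an event rate. Expected arm A enrolment is 30 to 37 over the three simulated scenarios, but the trial was already recruiting, so a change reaches anywhere from none to all of them. One mid-treatment scan narrows the gap without closing it. A reader might infer that day 15 is the optimal visit; that depends on an assumed onset curve. A reader might also suspect the efficacy result; nothing here touches pCR inference or the randomization. This is a cheap, minor safety improvement.

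**What to change.** Amend Table 1 for arm A patients still to be treated:

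- Move the routine EOS MUGA to an existing mid-treatment visit such as day 15 ± 3, with the reading available promptly enough to apply Table 4.
- Keep the EOT MUGA in both arms, as the between-arm LVEF comparison and the pre-surgery reading.
- Repeat MUGA at EOS in arm A if the mid-treatment or EOT reading is abnormal (below the LLN, or more than 20 % below baseline).
- Report the arm A-only on-treatment readings separately from the EOT comparison, and state how falls found only at that scan count toward the SAE stopping rule.
- Leave the Table 4 row and the arm B schedule unchanged.

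**Cost.** One amendment under the procedure in Ethical considerations. Arm A patients with normal readings still have three scans; those with an abnormal reading have four. The routine arm A post-surgery reading and the EOS between-arm comparison are lost, so a fall first appearing after EOT has no planned scan to find it. Falls after the mid-treatment scan are still found only at EOT. If the sponsor values the post-surgery reading more, adding the scan instead of moving it keeps that reading, at one extra scan per arm A patient.
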